**Five year follow-up:**
A journal audit and look-up in the Danish Health Data Authority will be performed to examine the number of clinical events according to the primary and secondary endpoints.

**Ten year follow-up**:
A journal audit and look-up in the Danish Health Data Authority will be performed to examine the number of clinical events according to the primary and secondary endpoints.

## Discontinuation:

Participants will be followed for the complete duration of the study regardless of their adherence to the study intervention. Any component of the study intervention may be discontinued at the discretion of either the participant or the study staff due to safety, behavioral or compliance reasons.

Withdrawal of consent: Participant may withdraw consent at any time upon request. Those considering withdrawal should be offered the option of flexible participation, if feasible. If a participant withdraws consent, any data collected before such a withdrawal of consent may still be used for study purposes. Participants who withdraw will be included as intention-to-treat in the statistical analysis once the study ends.

Lost to follow up: If participants fail to attend and complete the three years follow up visit, they will be considered lost to follow-up for the analysis of the secondary outcomes that requires attendance. However, these participants will still be included in the primary and secondary prognostic outcomes.

Timeline
The study started in January 2024, with a four-year inclusion period that will continue until January 2028. After three years, all patients will have a follow-up visit and baseline assessments will be repeated. Clinical events will be assessed at 5- and 10-years follow-up by journal audits and by look-up in the Danish Health Data Authority. Thus, the 5 years follow-up will be approximately in January 2031, and 10 years follow-up in January 2036 (figure 4).

**Figure 4 - Timeline for the study**

[figure not shown]

Outcomes The primary outcome is the time to the first occurrence of a composite of CV deaths, non-fatal myocardial infarction, non-fatal stroke, and hospitalization for heart failure.

The secondary outcomes are the time to the first occurrence of one of the single components of the primary outcome, and a combination of the single components of the primary outcome to assess the total symptom burden. Additional secondary outcomes will be the assessment of microvascular complications, protocol driven medical changes and a cost-effectiveness analysis of the Cardio Metabolic Clinic. Primary and secondary outcomes and endpoints are shown in the following table:

| **Primary outcomes** | **Primary endpoints** |
| --- | --- |
| To examine whether patients with type 2 Diabetes (T2D) receiving optimal diabetes care in a Cardio-Metabolic Clinic are superior compared to usual care in reducing; incidence of cardiovascular (CV) death, non-fatal acute myocardial infarction (AMI), non-fatal stroke, and hospitalization for heart failure (HF) | Time to the first occurrence of major adverse cardiovascular event (MACE), a composite endpoint consisting of:   - CV death - Non-fatal AMI - Non-fatal stroke - Hospitalization for HF |
| Units of measure: Measured in days. | Time frame: From baseline to 5 years of follow-up (FU). |

| **Secondary outcomes** | **Secondary endpoints** |
| --- | --- |
| To examine whether patients with type 2 Diabetes (T2D) receiving optimal diabetes care in a Cardio-Metabolic Clinic are superior compared to usual care in reducing; incidence of cardiovascular (CV) death, non-fatal acute myocardial infarction (AMI), non-fatal stroke, and hospitalization for heart failure (HF) | Time to the first occurrence of MACE, a composite endpoint consisting of:   - CV death - Non-fatal AMI - Non-fatal stroke - Hospitalization for HF |
| Units of measure: Measured in days. | Time frame: From baseline to 10 years FU. |
| To compare the individual component, CV death, of the primary endpoint in patients receiving optimal diabetes care in a Cardio-Metabolic Clinic versus usual care. | Time to the first occurrence of:   - CV death   (Presumed cardiac condition leading to death. Including: AMI, venous thromboembolic event, malignant arrhythmia, cardiogenic shock, fatal stroke and aorta dissection) |
| Units of measure: Measured in days. | Time frame: From baseline to 5 + 10 years of FU. |
| To compare the individual component, non-fatal AMI, of the primary endpoint in patients receiving optimal diabetes care in a Cardio-Metabolic Clinic versus usual care. | Time to the first occurrence of:   - Non-fatal AMI   Including: ST-elevation myocardial infarction, non-ST-elevation myocardial infarction |
| Units of measure: Measured in days. | Time frame: From baseline to 5 + 10 years of FU. |
| To compare the individual component, non-fatal stroke, of the primary endpoint in patients receiving optimal diabetes care in a Cardio-Metabolic Clinic versus usual care | Time to the first occurrence of:   - Non-fatal stroke   Including: Thromboembolic or undetermined |
| Units of measure: Measured in days. | Time frame: From baseline to 5 + 10 years of FU. |
| To compare the individual component, de novo HF and/or HF hospitalization, of the primary endpoint in patients receiving optimal diabetes care in a Cardio-Metabolic Clinic versus usual care | Time to the first occurrence of:   - De Novo Heart Failure - Heart Failure hospitalization |
| Units of measure: Measured in days. | Time frame: From baseline to 5 + 10 years of FU. |
| To assess the total symptom burden by a combination of the single component of the primary endpoints in patients receiving optimal diabetes care in a Cardio-Metabolic Clinic versus usual care | Number of overall symptom burden determined by summing the occurrences of:   - CV death - Non-fatal AMI - Non-fatal stroke - Hospitalization for HF |
| Units of measure: Measured in count of events. | Time frame: From baseline to 5 + 10 years of FU. |
| To compare the occurrence of microvascular complication, retinopathy, in patients receiving optimal diabetes care in a Cardio-Metabolic Clinic versus usual care | - Change in diabetic retinopathy stage based on eye examination (Fundoscopy) |
| Units of measure: Measured in ratio to baseline. | Time frame: From baseline to 3 years of FU. |
| To compare the occurrence of microvascular complication, nephropathy, in patients receiving optimal diabetes care in a Cardio-Metabolic Clinic versus usual care | - Change in estimated Glomerular Filtration Rate (eGFR)   Creatinine-based. |
| Units of measure: Measured in in ratio to baseline [mL/min/1.73 m^2]. | Time Frame: From baseline to 3 years of FU. |
| To compare the occurrence of microvascular complication, nephropathy, in patients receiving optimal diabetes care in a Cardio-Metabolic Clinic versus usual care | - Change in urinary albumin-to-creatinine ratio (UACR) |
| Units of measure: Measured in ratio to baseline. | Time Frame: From baseline to 3 years of FU. |
| To compare the occurrence of microvascular complication, nephropathy, in patients receiving optimal diabetes care in a Cardio-Metabolic Clinic versus usual care | - Change in Chronic Kidney Disease (CKD) stage   Calculated by eGFR and albuminuria. |
| Units of measure: Measured in ratio to baseline. | Time Frame: From baseline to 3 years of FU. |
| To compare the occurrence of microvascular complication, nephropathy, in patients receiving optimal diabetes care in a Cardio-Metabolic Clinic versus usual care | Time to first occurrence of a composite CKD endpoint consisting of:   - a decline in eGFR of more than 50%, - onset of end-stage kidney disease (dialysis, eGFR<15, kidney transplantation) - death from renal or CV causes |
| Units of measure: Measured in count of events. | Time Frame: From baseline to 3 years of FU. |
| To compare the occurrence of microvascular complication, liver fibrosis, in patients receiving optimal diabetes care in a Cardio-Metabolic Clinic versus usual care | - Change in fibrosis-4 (FIB-4).   FIB-4 is calculated using age, aspartate aminotransferase (ASAT), alanine aminotransferase (ALAT), and platelet count. |
| Units of measure: Measured in ratio to baseline. | Time Frame: From baseline to 3 years of FU. |
| To compare the occurrence of microvascular complication, liver fibrosis, in in high-risk patients receiving optimal diabetes care in a Cardio-Metabolic Clinic versus usual care | - Change in degree of liver fibrosis through a Fibro-scan |
| Units of measure: Measured in count of events. | Time Frame: From baseline to 3 years of FU. |
| To compare the occurrence of macrovascular complications, peripheral artery disease (PAD) and/or ischemic heart disease (IHD), in patients receiving optimal diabetes care in a Cardio-Metabolic Clinic versus usual care | Time to first occurrence of a composite macrovasucular endpoint comprising:   - new diagnosis of lower extremity arterial disease (LEAD), - new/progression of foot ulcers, - surgical procedures related to PAD - coronary revascularization   Surgical procedures includes: percutaneous transluminal angioplasty, peripheral artery bypass, thrombectomy, thrombolysis, amputations.  Coronary revascularization includes: percutaneous coronary intervention (PCI), coronary artery bypass graft. |
| Units of measure: Measured in count of events. | Time Frame: From baseline to 3 years of FU. |
| To compare the occurrence of macrovascular complications in the lower extremities, in patients receiving optimal diabetes care in a Cardio-Metabolic Clinic versus usual care | - Change in ankle-brachial pressure index (ABI) |
| Units of measure: Measured in ratio to baseline. | Time Frame: From baseline to 3 years of FU. |
| To compare change in protocol-driven medication in patients receiving optimal diabetes care in a Cardio-Metabolic Clinic versus usual care | Change in protocol-driven medication:   - Lipid lowering medication - Antihypertensive medication - Anti-thrombotic medication - Anti-diabetic medication - Nephro-protective medication |
| Units of measure: Measured in percentage [%]. | Time Frame: From baseline to 3 years of FU. |
| To compare change in patient experienced symptoms in patients receiving optimal diabetes care in a Cardio-Metabolic Clinic versus usual care | - Change in symptoms as reported by patients using the Kansas City Cardiomyopathy Questionnaire (KCCQ) |
| Units of measure: Measured in score points (change in percentage [%]). | Time Frame: From baseline to 3 years of FU. |
| To compare the net cost of implementing a Cardio-Metabolic Clinic in patients receiving optimal diabetes care versus usual care | - Net cost of a Cardio-Metabolic Clinic:  Cost of Cardio-Metabolic Clinic minus averted costs   Averted costs includes: averted admissions, medical treatment, and productivity). |
| Units of measure: Measured in dollars [$]. | Time frame: From baseline to 5 + 10 years of FU. |
| To compare the health outcomes of implementing a Cardio-Metabolic Clinic in patients receiving optimal diabetes care versus usual care | - Change in health outcomes measured by quality-adjusted life years (QALY) |
| Units of measure: Measured in score points (change in percentage [%]). | Time frame: From baseline to 5 + 10 years of FU. |
| To compare the cost-effectiveness of implementing a Cardio-Metabolic Clinic in patients receiving optimal diabetes care versus usual care | - Cost-effectiveness ratio of a Cardio-Metabolic Clinic: Net cost/change in health outcomes |
| Units of measure: Measured in $/QALY. | Time frame: From baseline to 5 + 10 years of FU. |

Statistics

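### The heart-failure row presented as a component of the primary endpoint also counts new heart failure without admission, and the stroke component is not defined in the same terms as the primary

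*Protocol*

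**What the plan says.** The Outcomes section of the protocol defines the primary as time to first occurrence of "a composite of CV deaths, non-fatal myocardial infarction, non-fatal stroke, and hospitalization for heart failure". It describes the first group of secondary outcomes as "the time to the first occurrence of one of the single components of the primary outcome". The outcomes table repeats the four primary items as "CV death - Non-fatal AMI - Non-fatal stroke - Hospitalization for HF", and the same four appear in the 10-year composite row and in the total-burden row.

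The HF component row departs from this. Its objective is "To compare the individual component, de novo HF and/or HF hospitalization, of the primary endpoint", and its endpoint is time to the first occurrence of "De Novo Heart Failure - Heart Failure hospitalization". The row gives no criteria or care setting for new HF.

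The non-fatal stroke component row adds "Including: Thromboembolic or undetermined". The primary row gives no stroke subtype. The cardiovascular death row lists its causes, among them "malignant arrhythmia, cardiogenic shock, fatal stroke and aorta dissection", again without a stroke subtype.

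**The concern.** Component analyses are there to show which events drive a composite result. That requires each component to be the event that enters the composite. If the HF row counts something more, its result cannot be read as the HF part of the primary, in either direction.

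The extra event is also of a softer kind. An admission leaves a record whichever arm the patient is in; a new diagnosis without admission depends on someone looking for it and writing it down. The row matters for formal inference too. The section on testing and confounders orders the tests by the succession of the objectives, and in the table this is the fifth secondary row, after 10-year MACE, cardiovascular death, myocardial infarction and stroke.

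For stroke, the question is whether a non-fatal haemorrhagic stroke counts. The clinic's treatment algorithm promotes antithrombotic treatment, so the plan should leave no doubt about it.

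**Working it through.** The protocol states no figure on this point, so there is nothing to reproduce. The check sets the definitions side by side.

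| Row in the outcomes table | HF event counted | Non-fatal stroke |
| --- | --- | --- |
| Primary, 5 years | Hospitalization only | No subtype given |
| MACE, 10 years | Hospitalization only | No subtype given |
| Total burden | Hospitalization only | No subtype given |
| HF component | New HF or hospitalization | – |
| Stroke component | – | Thromboembolic or undetermined listed |

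**What the HF row adds.** A new HF case that presents as an admission is already an HF hospitalization. The words on new HF therefore change the endpoint only through cases recorded without admission, or recorded before one. Eligibility admits patients with HF at any ejection fraction, and they cannot have new HF. The row thus measures admission only in those with HF at entry, and admission or diagnosis in the rest.

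**Whether recording can differ by arm.** The study design is open label. In the clinic arm a cardiologist reviews each risk profile and the recommended treatment, and individual visits are arranged when a new treatment needs monitoring. HF is also one of the algorithm's triggers for prescribing an SGLT2 inhibitor, so clinic staff need to know HF status. Against this, both arms have the same examinations at baseline and three years, and events at 5 and 10 years come from journal audit and register look-up. These limit the difference but do not remove it, because journals and registers hold only diagnoses that someone made.

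**Illustration of the sensitivity (assumed inputs).** Take a true hazard ratio (HR) of 0.85 for every HF event, borrowing the 15% reduction that the sample size section anticipates for the primary. Let s be the share of first HF events that are new HF without admission, and r the ratio of their recording, clinic to control. Neither is in the documents. Then

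observed HR = 0.85 × ((1 − s) + s × r)

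| s | r = 0.75 | r = 1 | r = 1.25 |
| --- | --- | --- | --- |
| 10% | 0.85 × 0.975 = 0.83 | 0.85 | 0.85 × 1.025 = 0.87 |
| 30% | 0.85 × 0.925 = 0.79 | 0.85 | 0.85 × 1.075 = 0.91 |
| 50% | 0.85 × 0.875 = 0.74 | 0.85 | 0.85 × 1.125 = 0.96 |

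The results lie on both sides of 0.85. The table shows that the row can move with recording, not that it will move a given way.

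**Stroke.** Two readings are open.
- The list may belong to the component row only. If it is also exhaustive, component and primary differ.
- The list may define stroke throughout. Cardiovascular death and myocardial infarction are likewise detailed only in secondary rows, so this is possible. Component and primary then agree, but if the list is exhaustive a non-fatal haemorrhagic stroke enters no listed clinical event outcome, because the table has no bleeding outcome.

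**The case against.** The strongest reply is that this is one mislabelled secondary row. The primary, the 10-year composite and the total-burden row all count HF by hospitalization, so the mismatch reaches none of them. That stands. It can also be said that the row never calls itself a composite, unlike the MACE, kidney and macrovascular rows, and that its two items could be meant as two endpoints reported separately. The wording permits this, but does not say it; even then, new HF is still presented as a component of the primary, which it is not.

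A reader might infer that the HF result is biased against the clinic because the clinic finds more HF. The documents do not support so firm a statement. They describe no HF work-up in the clinic arm and list no echocardiography; NT-proBNP is drawn in all participants at both scheduled visits; and control care may include the cardiology outpatient clinic. A difference in detection is plausible, but its size and direction are unknown.

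A reader might also infer that haemorrhagic stroke is excluded and that this favours the clinic. The row uses an inclusive word and excludes nothing expressly. The direction is also unproven: the same algorithm intensifies blood-pressure control, which could act the opposite way on haemorrhagic stroke.

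Finally, one might argue that the components ought to sum to the composite. They would not do so even with identical definitions, since one patient can have several types of first event.

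**Conclusion.** The HF point holds on the text. The row labelled as a component of the primary contains an event type that the primary does not, so it cannot serve as the HF part of that endpoint. It is open to differential detection, of unknown size and direction; the HRs of 0.74 to 0.96 above rest on assumed shares and recording ratios and are not estimates. The primary analysis is not affected. Because the protocol itself gives the two definitions, this is a contradiction to resolve and not a detail left to the analysis plan.

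The stroke point is lesser and conditional. What is certain is that the primary gives no stroke definition and that the component row names two types. Whether non-fatal haemorrhagic stroke is lost, and from which endpoints, depends on a reading that the protocol does not settle.

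**What to change.** 1. Define the HF component as time to first hospitalization for HF, exactly as in the primary, at 5 and 10 years.
2. Report new HF as a separate outcome, restricted to participants without HF at baseline, with its diagnostic criteria and source stated, and not labelled a component of the primary.
3. State one definition of non-fatal stroke and apply it to the primary, the 10-year composite, the total-burden count and the component. Preferably it covers all types, with a breakdown by type.

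This is a change of wording. The same journal audit and register look-up supplies the events, and the protocol places the 5-year look-up at about January 2031, so the definitions can be settled well before then. The downside is one additional outcome to report and, if all stroke types count, possibly some dilution of the stroke component.

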**Analysis of categorical outcome**
For each supportive categorical outcome, multivariable logistic regression with generalized estimating equations (GEE), allowing analysis of repeated measures, will be applied, including adjustment for baseline factors, which may contribute to the outcome variable. The model will deliver estimated adjusted odds ratio and 95% confidence interval.
Examples of supportive categorical outcomes: de novo/worsening retinopathy, nephropathy, hypertension and hypercholesterolemia.

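### Retinopathy stage and CKD stage are ordered categories, but the outcome table measures their change as a ratio to baseline; for retinopathy this conflicts with the planned categorical analysis

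*Protocol*

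**What the plan says.** The secondary-outcome table in the Protocol's Outcomes section has two rows whose endpoint is a stage:

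- Retinopathy: "Change in diabetic retinopathy stage based on eye examination (Fundoscopy", with the line "Units of measure: Measured in ratio to baseline" and a time frame from baseline to 3 years.
- Kidney disease: "Change in Chronic Kidney Disease (CKD) stage", derived from eGFR and albuminuria, with the same unit and time frame.

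In both rows the stated objective is to compare how often the complication occurs in the two arms.

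The section Analysis of categorical outcome says: "For each supportive categorical outcome, multivariable logistic regression with generalized estimating equations (GEE), allowing analysis of repeated measures, will be applied". The model is to deliver an adjusted odds ratio with a 95% confidence interval. The examples it gives are "de novo/worsening retinopathy, nephropathy, hypertension and hypercholesterolemia".

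The section Analysis of numerical outcome plans a mixed-effects linear model. Its example is change in biochemistry, and it names no stage variable.

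The Protocol states no grading scale and no numeric coding for either stage. The eligibility criteria require type 2 diabetes and heart or vascular disease; they do not require retinopathy or kidney disease.

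**The concern.** A ratio needs a scale with a true zero and equal units. A stage has neither: the numbers are labels for an order. Dividing the follow-up stage by the baseline stage therefore gives a result that depends on the labels chosen and on where the participant started.

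The outcome table and the analysis section also describe different outcomes for retinopathy. One is a quotient of stages. The other is a category, new or worse disease, summarised by an odds ratio. A ratio to baseline cannot be the response in a logistic model. An analysis plan that follows the table inherits an uninterpretable measure, and one that follows the analysis section departs from the endpoint unit in the Protocol. In an open-label trial, that choice should be settled before the three-year data are seen.

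**Working it through.** The Protocol gives no figure to reproduce on this point. The check has three parts.

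**1. What the ratio does to a one-stage change**

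Inputs: the unit (ratio to baseline) is from the outcome table. The coding is an assumption, because the Protocol gives none. Two five-level codings are shown, with no retinopathy coded 0 (stages 0–4) or coded 1 (stages 1–5).

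Formula: ratio = follow-up code / baseline code.

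| Change | None coded 0 | None coded 1 |
| --- | --- | --- |
| None to none | 0/0, undefined | 1/1 = 1.00 |
| None to first stage | 1/0, undefined | 2/1 = 2.00 |
| First to second | 2/1 = 2.00 | 3/2 = 1.50 |
| Second to third | 3/2 = 1.50 | 4/3 = 1.33 |
| Third to fourth | 4/3 = 1.33 | 5/4 = 1.25 |

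Under the first coding, no participant free of retinopathy at baseline has a value, so new onset cannot be scored. Under the second, every participant has a value, but the same one-stage worsening takes four different values. Neither coding gives one stage a fixed meaning.

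**2. What this can do to a comparison of arms**

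Take two hypothetical arms of 20. In arm A, 10 worsen from the first to the second stage and 10 are stable at the third. In arm B, 14 worsen from the third to the fourth stage and 6 are stable at the first.

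- Proportion worsening: A 10/20 = 50%; B 14/20 = 70%.
- Mean ratio, none coded 0: A (10 × 2.00 + 10 × 1.00)/20 = 1.50; B (14 × 4/3 + 6 × 1.00)/20 = 1.23.
- Mean ratio, none coded 1: A (10 × 1.50 + 10 × 1.00)/20 = 1.25; B (14 × 1.25 + 6 × 1.00)/20 = 1.175, or 1.18.

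Under both codings the mean ratio makes A look worse, although fewer of its participants worsened.

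These arms differ in baseline mix, which randomisation would tend to balance, so the example shows a mechanism and is not a forecast. The mechanism does not need the imbalance. With none coded 0, a worsening from the first stage adds 2.00 − 1.00 = 1.00 to the sum of ratios, and one from the third adds 1.33 − 1.00 = 0.33, a weight of 3 to 1. With none coded 1, the additions are 0.50 and 0.25, a weight of 2 to 1. The weights come from the labels alone.

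**3. The sections side by side**

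- Retinopathy: the table gives a ratio of stages, while the analysis section names new or worsening retinopathy as categorical. The conflict is explicit. The analysis section also presupposes participants without retinopathy at baseline, since new onset is possible only in them, and the eligibility criteria admit them.
- CKD stage: the analysis section names nephropathy and does not name CKD stage. The Treatment algorithm section defines nephropathy by eGFR below 60 ml/min and/or UACR above 30 mg/g, a yes/no definition. The conflict for CKD stage is therefore an inference.
- CKD stage, scale only: the row derives the stage from two measurements and defines no number to divide. This objection does not depend on the analysis section.

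**The case against.** The strongest reply is that the table supplies only a unit label. The Statistics section governs the analysis, and there retinopathy is already categorical. No analysis text uses a ratio of stages or says that anyone is dropped. The label was probably carried over from neighbouring continuous rows. Units are loose elsewhere in the table too: the eGFR row combines a ratio with mL/min/1.73 m², and some time-to-first-event composites are measured in counts of events.

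Much of this stands. It makes the categorical reading the more natural one and limits the damage. It does not make the label correct. The unit is part of the endpoint's stated definition, and it contradicts the analysis that the Protocol itself intends.

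A reader might infer more than the Protocol supports:

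- **That the ratio is undefined for everyone without retinopathy at baseline.** This is true only if no retinopathy is coded 0, and the Protocol gives no coding.
- **That a large, countable share of the 1500 participants would have no value.** The Protocol gives neither the coding nor the baseline frequency of retinopathy, so no count can be supported.
- **That the CKD-stage row openly contradicts the analysis section.** That section says nephropathy, and only as an example.
- **That a confirmatory, multiplicity-corrected result is at stake.** The section Testing and confounders orders the tests by the succession of the objectives and applies Bonferroni-Holm. The categorical outcomes are called supportive, and the Protocol does not say whether supportive outcomes belong to the corrected family.

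**Conclusion.** The point holds for both stage outcomes and should be corrected. Ratio to baseline is the wrong unit for an ordered stage under either coding examined: new onset has no value, or the same one-stage worsening ranges from 2.00 down to 1.25 by starting stage. The conflict with the planned categorical analysis is explicit for retinopathy and inferred for CKD stage.

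The numerical illustration rests on assumed five-level codings and hypothetical arms. The conclusion does not, because any numbering of ordered labels makes the quotient arbitrary. The consequence is confined to two secondary outcomes; the primary endpoint and the sample size are untouched.

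**What to change.** 1. Name the grading scale for retinopathy stage and for CKD stage, including how eGFR and albuminuria combine into one stage or category.
2. In these two rows, replace ratio to baseline with new onset or worsening by at least one stage or category from baseline to 3 years (yes/no).
3. Analyse both with the logistic model already planned for categorical outcomes, adjusted for baseline stage, and name CKD stage in that section.
4. Leave ratio to baseline for the continuous measures: eGFR, UACR, FIB-4 and ABI.

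A supporting ordinal model, or a log scale for the continuous ratios, is optional and can be left to the statistical analysis plan.

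The cost is a wording change to the outcome table and the analysis section, with no new data to collect. It should be made before the three-year data are examined. With a start in January 2024, the first three-year visits fall due in January 2027 at the earliest.
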